## 16. TREATMENT OF SUBJECTS

### 16.1 Investigational treatment

The treatment, or intervention, in our study is best described as withholding PN in the early course of disease to reach currently recommended energy and protein intakes, when enteral delivery of these intakes is insufficient. In both allocation groups of the study, patients will be evaluated on a day to day basis to see which amount of enteral intake can be provided. The “early PN” group will receive current standard nutritional practice, which prescribes that PN should be added to EN as soon as possible in the course of disease, to achieve energy and protein goals. In the “late PN” group, we will wait to add PN, when EN is insufficient, until day 7.

[figure not shown]

“Late PN”, the so-called “intervention-group”.

In Leuven, Rotterdam and Edmonton patients randomised to the “late PN” group will receive a mixture of Glucose 5% and NaCl 0.9% at, respectively, 60% and 40% of the total flow rate that is required to obtain standard optimal hydration taking into account the volume of EN that is being delivered. If enteral feeding of at least 80% of the calculated calories is not possible after 7 days in ICU, PN, as specified below, is initiated on day 8.

The infusions will be supplemented with micronutrients and vitamins as they would have received when provided PN.

When the blood glucose levels fall spontaneously below 50 mg/dl, the standard glucose of 5% in the late PN group will be switched to 10% glucose until blood glucose level is above 80 mg/dl. At this point the infusion of glucose 10% will be stopped and switched again to glucose 5%.

Early PN", this nutritional regime is the standard therapy in the participating centres and therefore accounts as the "control-group".

All centres will use their current pharmaceutical nutritional products for enteral as well as parenteral nutrition. The differences between the products provided by the different pharmaceutical companies are small clinically irrelevant differences in glucose, lipid and protein intakes.

Despite the different pharmaceutical companies, nutritional regimes from all participating centres will be aiming for the same energy and protein targets.

Fluid intake will be provided as follows; patients not requiring fluid restriction receive 100 ml/kg/day for the first 10 kg bodyweight, 50 ml/kg for the next 10 kg, and 20 ml/kg for the bodyweight over 20 kg, patients who require fluid restriction, total fluid intake is 50% on day 1 and 2, and 75% on day 3.

#### Nutritional target calculations

##### Energy intake

- < 10 kg bodyweight : 100 kcal/kg/day
- 10-20 kg bodyweight : 1000 kcal/day + (50 kcal/kg/day for weight over 10 kg)
- > 20 kg bodyweight : 1500 kcal/day + (20 kcal/kg/day for weight over 20 kg)

##### Protein target

- 0-10 kg bodyweight : 1.5-3 g/kg/day
- 10-20 kg bodyweight : 1-3 g/kg/day
- > 20 kg bodyweight : 1-2 g/kg/day

##### Day 1:

In the PICUs from all centers, patients randomised to the "early PN" group upon admission to PICU receive a glucose mixture [Leuven; Glucose15%/Vaminolact® (Fresenius), Rotterdam; Glucose 10–20% (Baxter)] to achieve glucose intake approximately double of the intake in the "late PN" group, with additional trace elements (Peditrace®) and minerals (Addamel®, Novum, Fresenius) and vitamins (Cernevite®, Soluvit®, Vitintra®; Baxter) to be administered in all centers.

##### Day 2-3:

For all patients on intravenous (IV) nutrition, lipids [Leuven; (20g/100ml) SMOFlipid® Fresenius, Sweden, Rotterdam; (20g/100ml) Intralipid® (Baxter), Oliclinomel® (Baxter)] are added from day 2-3 onward, and increased depending on the age and within the fluid limitation potentially required by the patient.

Additionally, protein intake [Leuven; Vaminolact® or Vamin18® (Fresenius, Sweden), Rotterdam; Primene® (Baxter), Oliclinomel® (Baxter)] will be increased to reach target goals.

On day 2-7, pharmacy-prepared PN preparations are prescribed to achieve protein and energy goals, as described above, unless adequate enteral nutritional intake is expected.

Any enterally delivered energy is taken into account twice daily to reduce the energy delivered by PN. When EN covers 80% of optimal calculated caloric needs, PN is stopped.

When the patient starts to take oral nutrition, the PN and/or EN is reduced and eventually stopped. Whenever enteral or oral intake falls below 50% of calculated caloric needs, the PN is restarted.

The volumes of PN and EN to be given according to the treatment group are calculated by the patient data management system (PDMS). These calculations are based on the nutritional intake during the previous day and the clinical evolution of the patient. The amount of protein and glucose administered during the previous day, as well as the target, will be displayed by the PDMS to further guide the prescription of macronutrients.

The additional trace elements (Peditrace®) and minerals (Addamel® Novum®, Fresenius) and vitamins (Cernevite®, Soluvit®, Vitintra®; Baxter) will be administered in all centers daily until patients receive at least 80% of their caloric intake enterally.

### ***Enteral nutrition and micronutrient administration***

In all patients from both study arms, provided haemodynamically stable and without formal contraindication, EN is initiated on the afternoon following the ICU admission with the patients in semirecumbent position. Enteral feeding will start 6 hrs after admission in the PICU and will be done according to protocol (cfr appendix 1). Trace elements (Peditrace®) and minerals (Addamel® Novum®, Fresenius) and vitamins (Cernevite®, Soluvit®, Vitintra®; Baxter) will be administered daily IV to all patients from day 2 at 4:00 pm. IV micronutrient substitution will be stopped when patients receive at least 80% of their caloric needs via the enteral route.

In infants, breast milk, the patient's home milk formula or a protein-energy dense formula (Nutrilon®, Infatrini®; Nutricia Netherlands) is used. Older children receive standard commercially available enteral feeding (Nutrison®, Nutrini-formulas; Nutricia Netherlands) unless contra-indicated.

Enteral feeding is administered through a gastric tube in a continuous way and is gradually increased as dictated by tolerance. Switch to oral intake is made as soon as deemed safe. The increase of EN volume, the use of gastroprokinetics and duodenal feeding tubes are described in standing-orders for EN. Procedures for slow parenteral administration will be identical for all patients.

### ***Blood glucose management***

Blood glucose management will be performed as through standard practice in all participating centers. (for protocols see the appendices)

In **Leuven**, patients in both study groups receive continuous insulin infusion to target blood glucose levels of 50-80 mg/dl when aged < 1y and 70-100 mg/dl when aged ≥ 1 year. Blood glucose and potassium are monitored systematically every 1 – 4 hours on the blood gas analyser (ABL Radiometer®, Copenhagen, Denmark) using arterial blood samples. (14)

In **Rotterdam**, patients in all age groups receive continuous insulin infusion to target blood glucose levels of 72-145 mg/dl, except for patients with traumatic brain injury (108-145 mg/dl), using a step-wise nurse driven glucose control protocol. Blood glucose and potassium are monitored systematically every 1 – 3 hours on the blood gas analyser (ABL 625; Radiometer®, Copenhagen, Denmark) using arterial blood samples. (15)

In **Edmonton** patients in all age groups receive continuous insulin infusion to target blood glucose levels <180 mg/dl

[figure not shown]

Nutritional protocol showing schematic decision tree

### ***Handling of re-admissions to ICU***

Patients who are re-admitted to ICU after a participation in PEPaNIC are not eligible for re-inclusion. Patients who are readmitted to the PICU within 48 hours of discharge and who are still within the 7 days time window of the initial randomization receive the nutrition-schedule they were assigned to during the initial ICU admission. Patients readmitted later will be fed at the discretion of the attending physician.

#### **16.2 Use of co-intervention (if applicable)**

Not applicable

#### **16.3 Escape medication (if applicable)**

Not applicable

### **17. INVESTIGATIONAL MEDICINAL PRODUCT**

Not applicable.

## 18. METHODS

### 18.1 Study parameters/endpoints

#### 18.1.1 Main study parameter/endpoint

The primary efficacy endpoints of for this RCT are included into **Work Package 1** and are the incidence of new infections and the time to discharge alive from ICU. Number of patients with new infections and types of infection will be assessed by numbers and percentages, and the duration of any antibiotics therapy initiated after randomization for those patients requiring antibiotics will be analyzed by non-parametrical tests. As the time of ICU discharge to the regular ward may be affected by the availability of beds on the regular wards, which could induce bias, we *a priori* decided to analyze “time to discharge from ICU” as “time to ready for discharge from ICU”. A patient is considered “ready for discharge” as soon as all clinical conditions for ICU discharge have been fulfilled (no longer in need for vital organ support). Time to discharge alive from ICU will be reported by Kaplan-Meier plots, with ICU non-survivors censored beyond the longest ICU stay of survivors and censoring time of patients still in the ICU at closing of the data file (90 days after last patient inclusion) over both treatment groups. The impact of “late PN” versus “early PN” will be analyzed, with and without correction for age, nutritional status and risk categories and type and severity of illness, by Cox proportional hazard analysis. The distribution of the actual time to discharge from ICU will be reported for ICU-survivors and ICU-non-survivors separately. In view of the time window of the randomized intervention in ICU, also the proportion of patients staying beyond 8 days in ICU will be reported.

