### **STUDY DESIGN**

This study is a large, three-centre, non-blinded, randomized, controlled study. The study intervention will last for a maximum of 7 days per patient, and the entire study (final patient completed study) is anticipated to last 4 years, excluding the long-term follow-up, the health-economic analysis and the completion of the mechanistic studies. (See figure)

Consecutive patients are randomly assigned to one of the two treatment study groups using a digital system with central, computerised randomisation. Randomisation – in a one to one allocation ratio - is performed per centre and using permuted blocks of 10 per diagnostic stratum. The block size remains unknown to bed-side physicians and nurses, responsible for patient recruitment and therapy assignment.

The “early PN” strategy will be the nutritional management currently applied in the participating centres, acting as “control”.

The “late PN” strategy comprises initiation of this strategy only after day 7 in PICU.

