### ***General rules of the statistical analysis***

All analyses will be done on intention to treat basis. The analyses will be performed on the whole set of patients and by subgroups of patients based on the primary diagnostic categories used as prognostic factors for stratification and on septic/non-septic groups of patients.

A consort diagram will be reported. The data file will be finalised 90 days after inclusion of the last patient. To assess compliance with the study protocol, the amounts of PN and EN actually given in the two study groups during the intervention window of 7 days will be reported as absolute numbers and percentages of target calories. Discrete variables will be summarised by frequencies and percentages and analysed by (exact) Chi- square test or logistic regression analysis. Continuous variables will be summarised by use of either mean or standard deviations (SD) or median and interquartile range as appropriate and compared using Student's t-test or Mann-Whitney-U test, as appropriate. Time to event analysis will be performed by Cox proportional hazard analysis. All outcomes will be analysed in an uncorrected manner as well as (jointly) corrected for risk factors (type and severity of illness, age, on admission nutritional status and risk scores). *A priori* defined subgroup analyses will be performed for patients admitted to ICU after cardiac surgery as compared with all other patients; for patients with and without sepsis upon admission; for patients with contra-indications for EN on admission or not. For all endpoints, differences will be considered statistically significant whenever the p-value is lower than 0.05 without correction for multiple testing.

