#### *Statistical analyses*

As the sample size of the present study depended on the number of undernourished children included in the PEPaNIC-trial, we plan to perform a retrospective power analysis based on observed differences for risk of new infection as primary endpoint, rather than performing an a priori sample size calculation.

Variables will be reported as percentages, means ( $\pm$ SD) if normally distributed or as medians (IQR) if not-normally distributed. Change in weight will be reported as change in WFA or BFA SD score. Proportions will be analyzed univariably using chi-square test, means with t-test and medians with Mann Whitney test. The time-to-event effect sizes will be estimated with use of Cox proportional-hazard analysis, with data censored at 90 days. To take into account death as a competing risk for outcomes related to duration of care, data for non-survivors will be censored at 91 days. These time-to-event outcomes will be analyzed adjusted for baseline risk factors treatment center, age, diagnosis group, STRONGkids category, PIM2 score and PELOD score. The multivariable analysis of the effect of the intervention on dichotomized outcomes, adjusted for baseline risk factors, will be performed using logistic regression. Analyses regarding change in weight will additionally be adjusted for malnourishment upon admission.

P-values  $\leq 0.05$  will be considered statistically significant. P-values for interaction were calculated with the use of multivariable logistic regression analyses and multivariable Cox proportional-hazard analyses with a threshold for significance of interaction set at  $P \leq 0.10$ .

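### The primary analyses leave out centre, a randomisation factor; separately, two uncorrected primary endpoints give about a 9%–10% chance of a false primary claim, or about 10%–14% if either model may count

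*Supplement*

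**What the plan says.** All references are to the final protocol unless the SAP is named.

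- **Randomisation.** The Study Design section says that allocation "is performed per centre and using permuted blocks of 10 per diagnostic stratum". Section 18.2 also describes blocks of 10 and lists the diagnostic categories, but does not name centre as a stratum.
- **Primary endpoints.** Section 18.1.1 says that these "are the incidence of new infections and the time to discharge alive from ICU". No order of testing is given, and nothing says whether one or both must succeed.
- **Models.** Section 18.1.1 specifies the Cox analysis of live discharge "with and without correction for age, nutritional status and risk categories and type and severity of illness, by Cox proportional hazard analysis". The general rules in section 20.1 widen this: "All outcomes will be analysed in an uncorrected manner as well as (jointly) corrected for risk factors", the factors being "type and severity of illness, age, on admission nutritional status and risk scores". Centre is in neither list, and neither model is called primary.
- **Decision rule.** Section 20.1: "For all endpoints, differences will be considered statistically significant whenever the p-value is lower than 0.05 without correction for multiple testing".
- **SAP.** Its Statistical analyses section adjusts time-to-event outcomes for "treatment center, age, diagnosis group, STRONGkids category, PIM2 score and PELOD score". By its own aims, this SAP covers a later secondary analysis in undernourished children.

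**The concern.** The analysis should reflect the way patients were randomised. Blocking within centre and diagnosis balances the arms on those factors, so the true variability of the treatment difference is smaller than a plain two-group test assumes. Ignoring the factors wastes that gain. This matters most for infection, where the protocol claims only 70% two-tailed power.

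The second issue would exist even if centre were in every model. Two primary endpoints at 0.05 each, with nothing said about whether one suffices, leave the overall error rate of the primary claim undefined. Reporting each endpoint under two models, with none designated, also allows a choice after the results are seen.

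**Working it through.** **1. The protocol's own power figure.** Inputs from section 15.4: 720 per arm, infection 20% v 15%.

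- Pooled SE = √(2 × 0.175 × 0.825 / 720) = 0.02003. Unpooled SE = √((0.16 + 0.1275) / 720) = 0.01998.
- Two-sided: (0.05 − 1.960 × 0.02003) / 0.01998 = 0.54, so power is 70.5%.
- One-sided: (0.05 − 1.645 × 0.02003) / 0.01998 = 0.85, so power is 80.3%.

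Both stated figures (70% and 80%) reproduce.

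**2. Effect of leaving centre out of the uncorrected infection test.** The documents give neither infection rates nor enrolment by centre. Assumed: centre sizes 640/640/160, exact 1:1 balance within centre, no treatment effect. The plain test uses p(1−p) from the pooled rate; the true variance uses the size-weighted mean of p(1−p) within centres.

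| Assumed centre rates | Pooled p(1−p) | Within-centre mean | Ratio | Size by formula | Size simulated (400,000 trials) |
|---|---|---|---|---|---|
| 20/20/20% | 0.1600 | 0.1600 | 1.000 | 5.0% | 5.0% |
| 15/25/20% | 0.1600 | 0.1578 | 0.986 | 4.8% | 4.8% |
| 10/30/20% | 0.1600 | 0.1511 | 0.944 | 4.4% | 4.4% |

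Example, third row: (640 × 0.09 + 640 × 0.21 + 160 × 0.16) / 1440 = 0.1511. The effective critical value is 1.960 / √0.944 = 2.017, which gives a two-sided size of 4.4%. A deliberately extreme spread (5/40/20%) gives 3.2% in simulation. In every case the omission lowers the error rate. In the second and third rows the plain test overstates the variance by 1.4% (0.1600 / 0.1578) and 5.9% (0.1600 / 0.1511).

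**3. Two endpoints, one model.** If independent, 1 − 0.95² = 9.75%. With correlated normal test statistics (2,000,000 draws, |z| > 1.96), the figure is 9.1% at correlation 0.5 and 8.3% at 0.7.

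**4. Two endpoints, either model counting.** Same simulation with four statistics. The correlations are assumptions.

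| Model correlation | Endpoint correlation 0 | Endpoint correlation 0.5 |
|---|---|---|
| 0.90 | 13.6% | 12.6% |
| 0.95 | 12.5% | 11.6% |
| 0.99 | 11.0% | 10.2% |

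**5. After correction.**

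- At 0.025 per endpoint with one named model: 1 − 0.975² = 4.9% if independent, 4.6% at correlation 0.5.
- At 0.025 with both models still allowed (model correlation 0.90): 7.1% at endpoint correlation 0 and 6.7% at 0.5. Splitting alpha without naming a model is therefore not enough.
- Infection power at two-sided 0.025: (0.05 − 2.241 × 0.02003) / 0.01998 = 0.26, so 60.1%.
- Restoring 70% would take 883 per arm; 80% would take 1,097 per arm.

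**The case against.** **On centre.** Arms are balanced within centre by design, so omitting it introduces no bias. The corrected model includes type of illness, which plausibly covers the diagnostic stratum and leaves only centre missing there. Both statements stand.

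The documents' evidence that centres differ is mixed. Section 15.1 gives mean stays of 5.5 and 7.8 days, but for all 2010 admissions at two of the three centres, and the medians run the other way (3 and 2 days). The differing insulin targets in section 16.1 show different practice, not a known effect on either endpoint.

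A reader might put the cost at 1–4 points of power. That figure comes from a simulation that ignores all 42 centre-by-diagnosis strata, with an assumed between-stratum SD of 0.5–1.0 on the log-odds scale. It is not the effect of omitting centre.

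A reader might also infer from the SAP that the protocol is out of line with the trial's own plan. The SAP was written for a secondary analysis after the main results were known, so it shows only that adjusting for centre is feasible.

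**On multiplicity.** The lack of correction is stated openly, and infection and length of stay are distinct clinical questions for which separate claims can be defended. The protocol never says that significance in either model makes a primary claim. If both endpoints had to succeed in one named model, the error rate could not exceed 5%. These arguments lower the severity but leave the gap: neither a success rule nor a primary model is written down.

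**Conclusion.** Both points hold, as separate should-fix items.

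1. Centre is a randomisation factor that no primary analysis in the protocol uses. The consequence is a slightly conservative test and a modest loss of precision. The 4.4%–5.0% rests on assumed centre rates and sizes.
2. Two uncorrected primary endpoints give about 9%–10% familywise error under the global null, for assumed endpoint correlation 0–0.5. The 10%–14% applies only on the inferred reading that either model may count, with assumed model correlation 0.90–0.99.

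It is tempting to link the two and say that leaving out centre contributes to the inflated error rate. The documents do not support that: the omission pushes the error rate down, and the inflation comes entirely from the number of endpoints and models.

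**What to change.** - **Name one primary analysis per endpoint:** logistic regression for infection and Cox regression for live discharge, each containing centre, diagnostic stratum, age, nutritional risk category and severity. Label the uncorrected analysis supportive. This also removes the second-model part of the error rate. The small cost is that the odds ratio and hazard ratio become conditional on these covariates, which the report should say.
- **Reconcile the two descriptions of randomisation** (Study Design and section 18.2), so that it is clear that centre is a stratum.
- **Settle the two endpoints in writing.** Either declare them separate claims and state the familywise error of about 9%–10%, or apply Holm or Hochberg at overall two-sided 0.05. The second option controls the error but is a real trade-off: when infection has to be tested at 0.025, its power falls from about 70% to about 60% at the planned size. Adjustment may recover some of this, but the amount cannot be derived from the documents.

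Apart from that power cost, this is a change of wording only.

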#### 18.1.2 Secondary study parameters/endpoints

##### Work Package 1

All analyses will be performed uncorrected as well as corrected for age, nutritional status and risk categories and type and severity of illness. Time-to-event analysis will be analyzed similarly as the primary endpoint. Proportion of patients requiring support of vital organ functions and distribution of duration of support will be analyzed by non-parametric or parametric testing depending on the normality of the distribution in the subgroup of patients for which support was needed. Proportions will be compared using chi-square testing. Results of repeated measurements will be analyzed using an appropriate model for longitudinal data.

a. Time to final (alive) weaning from mechanical respiratory support: patients still on

mechanical respiratory support at closing of the data file (90 days after last patient

inclusion) will be censored at that time point. ICU non-survivors will be censored

beyond the longest duration of mechanical respiratory support of the survivors.

b. Kidney failure: Proportion of patients in need for renal replacement therapy (RRT)

during ICU stay; distribution of duration of RRT (for those patients requiring RRT);

proportion of patients with a post-randomization diagnosis of new kidney injury/failure

(defined by modified Risk, Injury, Failure, Loss, and End-stage Kidney (RIFLE)

classification criteria as a plasma creatinine doubling or more during ICU stay) in both treatment groups. In addition, the duration of a score RIFLE $\geq$ 2 will be used as a marker of time to recovery of kidney damage.

c. Need for pharmacological or mechanical haemodynamic support during ICU stay, and duration of such need.

In addition, time to final (alive) weaning from all pharmacological or mechanical haemodynamic support in ICU will be analyzed, with ICU non-survivors censored beyond the longest duration of pharmacological or mechanical haemodynamic support of the survivors and censoring time of patients still on such support at closing of the data file (90 days after last patient inclusion) over both treatment groups.

d. Number of readmissions to the PICU.

e. Liver dysfunction: Proportion of patients during the time window of the intervention and during the whole ICU stay presenting with cholestatic or cytolytic liver dysfunction will be compared.

f. Inflammation: Effect of the intervention on inflammation will be analyzed by comparing the distribution of the highest value reached during ICU stay and changes from baseline to the highest value and by comparing time profiles of daily C-Reactive Protein values.

g. Child health questionnaire scores in both treatment groups will be compared at 3 and 12 months post-discharge.

h. Enteral nutrition (EN) tolerance: proportion of patients with diarrhoea, high gastric residual volumes, vomiting and/or abdominal swelling and relation with buccal epithelial cell expression of chemokines (CXCL-8, CXCL-9 and CXCL-10)

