## **20.3 Multivariate analysis**

All outcomes will be analyzed in an uncorrected manner as well as (jointly) corrected for risk factors (type and severity of illness, age, on admission nutritional status and risk scores). Another *a priori* defined subgroup analysis will be performed for patients admitted to ICU after cardiac surgery as compared with all other patients. Also an *a priori* subgroup analysis is planned for patients with and without sepsis upon admission.

All analyses will be performed uncorrected as well as corrected for age, nutritional status and risk categories and type and severity of illness. Time-to-event analysis will be analyzed similarly as the primary endpoint. Proportion of patients requiring support of vital organ functions and distribution of duration of support will be analyzed by non-parametric or parametric testing depending on the normality of the distribution in the subgroup of patients for which support was needed. Proportions will be compared using chi-square testing. Results of repeated measurements will be analyzed using an appropriate model for longitudinal data.

a. Time to final (alive) weaning from mechanical respiratory support: patients still on mechanical respiratory support at closing of the data file (90 days after last patient inclusion) will be censored at that time point. ICU non-survivors will be censored beyond the longest duration of mechanical respiratory support of the survivors.

b. Kidney failure: Proportion of patients in need for renal replacement therapy (RRT) during ICU stay; distribution of duration of RRT (for those patients requiring RRT); proportion of patients with a post-randomization diagnosis of new kidney injury/failure (defined by modified Risk, Injury, Failure, Loss, and End-stage Kidney (RIFLE) classification criteria as a plasma creatinine doubling or more during ICU stay) in both treatment groups. In addition, the duration of a score RIFLE $\geq$ 2 will be used as a marker of time to recovery of kidney damage.

c. Need for pharmacological or mechanical hemodynamic support during ICU stay, and duration of such need.

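### Antibiotic and RRT durations are tested only among children who came to need treatment, with no all-randomised comparison and no rule for deaths

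*Supplement*

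**What the plan says.** All references are to the final protocol unless stated.

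- **Antibiotics (18.1.1).** The text reads: "the duration of any antibiotics therapy initiated after randomization for those patients requiring antibiotics will be analyzed by non-parametrical tests". No other analysis of antibiotic duration is listed.
- **RRT (18.1.2, repeated in 20.3).** The kidney item begins "Kidney failure: Proportion of patients in need for renal replacement therapy (RRT" and goes on to "distribution of duration of RRT (for those patients requiring RRT". For the first part, "Proportions will be compared using chi-square testing". The second part has no all-randomised version.
- **General rule for organ support (18.1.2 and 20.3).** Duration is tested parametrically or non-parametrically "depending on the normality of the distribution in the subgroup of patients for which support was needed".
- **Ventilation and haemodynamic support (18.1.2).** These have a further analysis. One endpoint is "Time to final (alive) weaning from mechanical respiratory support"; for the other, "time to final (alive) weaning from all pharmacological or mechanical haemodynamic support in ICU will be analyzed". In both, children who die in the ICU are censored later than the longest duration seen in any survivor, so an early death cannot pass for early recovery.
- **General rules (under 20.1).** "All analyses will be done on intention to treat basis", and p below 0.05 counts as significant for every endpoint, without multiplicity correction.

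The SAP covers a later analysis of undernutrition and weight change. Its outcomes include neither antibiotic nor RRT duration, so it does not settle the matter.

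**The concern.** Whether a child is started on antibiotics after randomisation is itself an outcome. Work Package 3 in 18.1.2 predicts fewer infections with late PN, and the Primary Objective puts the change at 20% to 15%. If that is right, allocation decides in part who enters the antibiotic comparison, and the two sets of treated children are no longer alike by design. Should late PN mainly prevent milder infections with shorter courses, the children still treated under late PN would have longer courses on average, although no child was worse off.

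Adjusting for baseline risk factors, as the plan also proposes, does not restore the randomised comparison, because the selection acts through an event after baseline. Death adds a second problem. A child who dies on treatment has a short recorded duration, and nothing says how that is to be counted for antibiotics or RRT.

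At stake is a p-value for a non-primary measure that could be read as a treatment effect when it partly reflects who was treated. It also sits badly with the plan's declaration of intention to treat.

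**Working it through.** **The plan's own figure.** Section 15.4 gives 720 per arm, 20% vs 15% infected, 5% level, power of at least 80% one-tailed and 70% two-tailed. With pooled proportion 0.175:

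- SE under no difference = √(2 × 0.175 × 0.825 / 720) = 0.02003
- SE under the alternative = √((0.20 × 0.80 + 0.15 × 0.85) / 720) = 0.01998
- One-tailed: Φ((0.05 − 1.645 × 0.02003) / 0.01998) = 80.3%
- Two-tailed: Φ((0.05 − 1.960 × 0.02003) / 0.01998) = 70.5%

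Both reproduce. This point disputes no stated number; the 20% and 15% are used below as planning rates.

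**Illustration.** Assumptions not in the documents: infection stands in for antibiotic need; under early PN 5% of children have 5-day courses and 15% have 10-day courses; late PN prevents the 5-day courses and changes nothing else.

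| | Early PN | Late PN | Late minus early |
|---|---|---|---|
| Mean among treated | (5 × 5 + 15 × 10) / 20 = 8.75 d | (15 × 10) / 15 = 10.0 d | +1.25 d |
| Mean per randomised child | 175 / 100 = 1.75 d | 150 / 100 = 1.50 d | −0.25 d |

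The plan specifies rank tests, and the medians among treated children are 10 days in both arms, so the ranks need checking too. The chance that a late-PN value exceeds an early-PN value, counting ties as half, is:

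- Among treated: 0.25 + 0.5 × 0.75 = 0.625. Above 0.5, so late PN looks longer.
- Among all randomised: 0.15 × 0.85 + 0.5 × (0.85 × 0.80 + 0.15 × 0.15) = 0.1275 + 0.3513 = 0.479. Below 0.5, so late PN looks shorter.

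**How often the test would mislead.** In a simulation with 720 per arm and log-normal courses (log-SD 0.4), the remaining courses had a median of 10 days and the prevented ones a median of 4 days. Median duration among treated children was 8.5 (early) vs 10.0 (late) days. The Mann-Whitney test was significant in the wrong direction in about 88% of 2,000 runs. Mean days per randomised child were 1.84 vs 1.63. Varying the assumed length of the prevented courses (500 runs each):

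| Median of prevented courses, days | 3 | 4 | 5 | 6 | 8 | 10 |
|---|---|---|---|---|---|---|
| Significant in the wrong direction | 91% | 85% | 75% | 55% | 15% | 2% |

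At 10 days the prevented courses match the rest, and only chance findings remain. Over the same range, a rank test on all randomised children favoured late PN significantly in 53% to 67% of runs. Deaths were not simulated.

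**RRT.** The documents give no RRT rate and no expected effect on RRT, so no corresponding figure can be computed.

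**The case against.** The strongest reply is that nobody would read these durations alone. If late PN prevented infections, the primary endpoint would show it over all randomised children, next to the durations. For RRT, the proportion needing it and the proportion with new kidney injury are also compared, and mortality is analysed separately. That stands. A reader might infer that the plan would report harm where there was only benefit; the documents do not support this, because the infection result would be in view.

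Four other strong readings also fail:

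- **All organ-support durations are compared only among users.** Ventilation and haemodynamic support have time-to-alive-weaning analyses with a death rule. What remains there is that the protocol does not say whether children never on support enter them.
- **Late PN is expected to change the need for RRT or haemodynamic support.** A direction is stated only for infections.
- **Antibiotic duration is a primary endpoint.** Section 18.1.1 describes it, but names only new infections and time to live ICU discharge as primary.
- **The cost results are biased.** Work Package 2 builds costs from volumes of care and invoices, by intention to treat. Its hypothesis about antimicrobials does not rest on durations among users.

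It is also fair to say that the size of any reversal depends on assumed course lengths, and that infection is not the same as starting any antibiotic. What does not stand is a defence that these durations are merely descriptive: antibiotic duration is explicitly tested, and the 0.05 threshold covers every endpoint.

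**Conclusion.** The point holds for two non-primary measures. Antibiotic and RRT durations are tested in subsets formed after randomisation, without an all-randomised comparison and without a rule for deaths. For antibiotics, the plan's own hypothesis implies that the subset differs by arm, so the test cannot be read as a treatment effect. For RRT, the same selection is possible but not predicted.

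A reversal is possible, not expected. In the illustration late PN looks 1.25 days worse among treated children while being 0.25 days better per randomised child. This rests on three assumptions: infection stands in for antibiotic need, late PN prevents shorter courses, and it leaves the other courses unchanged. When prevented courses are as long as the rest, the effect disappears.

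**What to change.** 1. For antibiotics and RRT, make the tested comparison over all randomised children. Use in-ICU days of treatment, with zero for no need and an explicit rule for deaths. One option is days alive and free of treatment to a fixed day within the 90-day follow-up, with death before that day scored as zero free days.
2. State how days after ICU discharge count. Section 18.3 registers medications during the ICU stay, and 15.4 plans for a shorter stay, so recorded days could differ by arm for that reason alone.
3. Report durations among treated children as description, without a p-value.
4. For the two weaning analyses, state that all randomised children enter them, and how those never on support are counted.

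**Cost.** Only wording changes. Days on antibiotics and on RRT are already recorded (18.3), and 90-day vital status is collected for all children (22.1). The downside is that a free-days measure mixes death with duration, so deaths should be shown alongside.
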